The required sample size was calculated using an estimated effect size (Cohen *d*) of 0.42, derived from a previous intervention study in South Sulawesi, which assessed the effects of *M. oleifera* supplementation on oxidative stress biomarkers in pregnant women exposed to passive smoking [37]. The study reported a mean difference in 8-OHdG levels between treatment groups of approximately 12.96 ng/mL with a pooled SD of ~30.68 ng/mL, yielding a moderate effect size. Using a 1-sided test with *α*=.05 and 80% power, the minimum required sample size is 37 participants per group. To account for an anticipated 20% dropout rate, the sample size was increased to 44 participants per group, yielding a total of 88 participants.

Approximately 200 pregnant women attending routine antenatal care (ANC) visits at the community health centers were sequentially approached and invited to participate in the study. They were first interviewed to determine eligibility based on inclusion and exclusion criteria. Those meeting the criteria were provided with detailed information about the study and asked to provide written informed consent. Following consent, a blood sample was collected to assess baseline levels of heavy metals.

Only participants with elevated levels above reference thresholds were considered eligible for inclusion in the intervention phase. For the intervention group, eligible participants were contacted and provided with *M. oleifera* supplements along with instructions for daily consumption over a 2-month period. They were informed that a follow-up blood collection would occur at the end of the supplementation period during a routine visit.

For comparison, the control group was recruited from a different health center in a separate subdistrict administrative unit that did not receive moringa supplementation. This approach minimized contamination between groups and allowed for feasible implementation of the intervention. Follow-up blood sampling was also conducted after 2 months, aligned with their next scheduled antenatal visit, but without providing moringa supplementation.

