### Data Analysis

All analyses will be conducted using the R statistical software (latest version). Data entry and cleaning will be conducted by trained staff using a double-entry verification. For 24-hour food recall data, participants will be asked to estimate portion sizes using visual aids, and data will be reviewed during collection for completeness and clarity. For the FFQ, if participants leave implausible answers (eg, extremely high frequency), the data will be reviewed and clarified during the interview or excluded from analysis after documentation. Implausible intake frequency will be cross-checked with interview notes and food recall summaries to determine plausibility. An intention-to-treat (ITT) analysis will be performed to preserve the benefits of initial group allocation. For missing or partial responses, multiple imputation will be considered for covariates in the adjusted models. For missing outcome data at follow-up, last observation carried forward (LOCF) will be used when feasible. Sensitivity analyses will be conducted to assess the robustness of findings under different missing data assumptions. Outliers will not be automatically excluded unless clear reporting errors are confirmed. Outliers in biomarker measurement will be identified using the interquartile range method and retained unless proven to result from analytic error or sample contamination. All statistical analyses will be conducted with and without outliers to assess the robustness of the results.

Descriptive statistics will summarize participant characteristics. All continuous variables, including heavy metal concentrations and biomarker levels, will be checked for normality before analysis. In the case of non-normal distributions, appropriate data transformations (eg, log transformation) will be applied. If normality cannot be achieved, nonparametric tests (eg, Mann–Whitney *U* or Wilcoxon signed-rank test) will be used as alternatives. Analysis of group differences (pre- and postintervention). For each group, analysis will be conducted using the paired *t* test or Wilcoxon signed-rank test, depending on data distribution, to assess changes in heavy metals, MDA, and 8-OHdG levels before and after intervention. The significance level (alpha) will be set at .05, and all tests will be one-tailed.

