For comparison between the groups (intervention vs control), analysis will be conducted using the difference-in-differences (DiD) method to measure the difference in changes between the intervention and control groups. The results will provide an overview of the impact of moringa leaf supplementation on the reduction of heavy metal levels and prevention of DNA damage in pregnant women. To address potential selection bias and confounding due to the nonrandomized design, we will use analysis of covariance (ANCOVA) to adjust for baseline differences in key variables such as maternal age, gestational age, education level, and baseline levels of heavy metals, MDA, and 8-OHdG.

Assumptions for ANCOVA will be checked using diagnostic plots and tests. Normality of residuals will be checked using the Shapiro–Wilk test and Q-Q plots. The homogeneity of variance test will use the Levene test from the car package. Linearity and homoscedasticity will be checked using residual versus fitted plots.

The interaction effects between intervention status and baseline heavy metal levels will be examined by adding interaction terms to the ANCOVA models. Additionally, stratification will be considered a sensitivity analysis to minimize bias. Baseline heavy metal levels will be included as covariates in the statistical models to account for variation in environmental exposure across recruitment areas. In addition, we will conduct exploratory subgroup analyses to assess potential effect modifiers. Outcomes will be examined separately for each heavy metal to assess whether the reduction effect of *M. oleifera* differs by metal type. Additional exploratory subgroup analyses may include stratification by trimester of pregnancy, nutritional status (BMI), and geographic location/pollution source.

If substantial differences are observed, these findings will be interpreted cautiously due to limited statistical power. All subgroup analyses will be considered hypothesis generating and reported transparently. If no significant interaction is found, primary analyses will focus on aggregate outcomes across all participants. Reduction in each individual heavy metal will be reported separately, along with a composite index. No interim analyses or stopping rules are planned due to the short duration of the trial and the nature of the design.

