### Expected Outcomes

#### Reduction in Blood Heavy Metal Levels

The primary outcome of this study is the reduction in blood Pb/Cd/Hg level. The hypothesis is that supplementation with *M. oleifera* will result in a reduction in the blood levels of heavy metals in pregnant women compared to those in the control group. Hence, the expected results are as follows: (1) A measurable decrease in the blood Pb/Cd/Hg concentration will be observed in the group receiving *M. oleifera* supplementation for 2 months. (2) The intervention group is expected to show a greater reduction in blood heavy metal levels than the control group, based on pre- and post-test analyses.

Scientific implications expected are that the result would provide evidence that *M. oleifera* has the potential to detoxify, thereby demonstrating that it is a safe and effective approach to reducing heavy metal accumulation in expectant mothers, who are at a higher risk of exposure to environmental pollutants.

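### The inputs given for 37 per group do not yield 80% power for the two-group comparison: unadjusted they need 71 per group, and 37 gives about 56%

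*Protocol article*

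**What the plan says.** The Participant Recruitment section uses an "estimated effect size (Cohen *d*) of 0.42". It derives this from an earlier moringa study in pregnant women exposed to passive smoking, which reported "a mean difference in 8-OHdG levels between treatment groups of approximately 12.96 ng/mL with a pooled SD of ~30.68 ng/mL". The design settings follow: "Using a 1-sided test with *α*=.05 and 80% power". The result is stated as "80% power, the minimum required sample size is 37 participants per group", and this is raised to 44 for 20% dropout. No test or formula is named, and no pre-post correlation is given.

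The same section elsewhere plans 59 women per group, and the Results overview reports that 26 per group have participated.

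Under Data Analysis the groups are compared by difference-in-differences, described as a "method to measure the difference in changes between the intervention and control groups", with ANCOVA to adjust for baseline. Paired tests within each group are planned as well. On the error rate the section says: "The significance level (alpha) will be set at .05, and all tests will be one-tailed".

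Under Expected Outcomes, "The primary outcome of this study is the reduction in blood Pb/Cd/Hg level", and the hypothesis there is a reduction relative to the control group. The Abstract places the oxidative stress markers, 8-OHdG among them, as secondary.

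**The concern.** Every stated input describes a comparison of two independent groups: a difference between treatment groups, a pooled SD, and a size quoted per group. For such a comparison 37 is far too small at d = 0.42. If the number is wrong, the article claims 80% power for its central contrast when the unadjusted power is little better than a coin toss. A reader who trusts the claim would give a null between-group result more weight than it deserves.

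The calculation is also presented as the study's required sample size, although it concerns a secondary marker. Nothing in it bears on the blood metals, which are the primary outcome.

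**Working it through.** **Inputs** (Participant Recruitment): difference 12.96 ng/mL, pooled SD 30.68 ng/mL, one-sided alpha .05, power 80%, equal groups. Data Analysis confirms one-tailed testing at .05.

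**Effect size.** 12.96 / 30.68 = 0.422, stated as 0.42. This reproduces.

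**Reproducing 37.** A one-sample or paired calculation uses n = ((z₀.₉₅ + z₀.₈₀)/d)² = ((1.645 + 0.842)/0.42)² = 35.05, or 36 after rounding up. The exact t version gives 36.4, so 37, with 80.5% power at 37. The stated figure therefore coincides with the one-sample/paired t result.

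**Two-group requirement.** n per group = 2((z₀.₉₅ + z₀.₈₀)/d)² = 2 × 35.05 = 70.1, so 71. The exact two-sample t test gives 70.8, also 71. With the unrounded d of 0.4224 it is 70. Allowing for 20% dropout, 71/0.80 = 88.75, or 89 per group, against the stated 44.

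**Unadjusted two-group power** (two-sample t test, one-sided .05, d = 0.42):

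| n per group | Where the size appears | Power |
|---|---|---|
| 26 | Results, participated | 44% |
| 37 | Participant Recruitment, minimum | 56% |
| 44 | Participant Recruitment, with dropout | 62% |
| 59 | Participant Recruitment, planned | 73% |
| 71 | Recomputed requirement | 80% |

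**Effect of the planned analyses.** The article states no pre-post correlation r, so a range is needed. Here I assume that 30.68 is the SD of raw values. ANCOVA then works with d/√(1 − r²), and a change-score difference-in-differences with d/√(2(1 − r)). Required n per group for 80% power, from the t test:

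| Assumed r | ANCOVA | Change-score DiD |
|---|---|---|
| 0.3 | 65 | 99 |
| 0.5 | 54 | 71 |
| 0.7 | 37 | 43 |

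By the normal approximation, 37 per group reaches 80% power only when r is about 0.69 (ANCOVA) or 0.74 (change score).

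**Outcome.** The difference and SD are both for 8-OHdG. No effect size, SD or sample size is given for Pb, Cd or Hg.

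**The case against.** **The within-group test belongs to this trial.** The Introduction words the hypothesis as lower levels than before supplementation, and Data Analysis plans paired tests. A reader might therefore infer that the authors used a paired formula, and that 37 is right for the paired test. Neither step is supported. The article names no test, so the formula is inferred only from a numerical match. A paired test also needs the SD of within-woman changes, whereas 0.42 is a between-group difference over a pooled SD. So 37 is not justified for the within-group tests either.

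**The unadjusted t test is not the planned analysis.** This stands. The 71 and the 56% are conditional on no baseline adjustment, and a reader should not take 71 as the size that this trial needs. With ANCOVA and r = 0.5, for example, 54 completers per group would do, which 59 would cover before dropout. A change-score analysis at r = 0.3 would need 99. If 30.68 is an SD of changes, the conversions above do not apply; that depends on the cited study. None of this rescues the 80% claim, because the article states no correlation on which it could rest.

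**The article already concedes limited power.** The Discussion lists limited sample size among the explanations for a null result and calls the findings hypothesis-generating. Strengths and Limitations calls them preliminary. This softens the consequence, and it would be too strong to say that a null result will be misread. But these are general remarks, directed mainly at small effects and subgroups. They do not correct the 80% figure for an effect that the article calls moderate.

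**Borrowing 8-OHdG is disclosed and understandable.** The article names the marker and the source population, and says that human evidence on moringa and metals is limited. The choice is not an error in itself. What is missing is a statement that the calculation does not cover the primary outcome.

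**Conclusion.** The concern holds in this form: 37 per group does not follow from the article's own inputs as a two-group number. Unadjusted, d = 0.42 at one-sided .05 requires 71 per group, nearly twice the stated figure. Power is about 56% at 37, and none of 26, 37, 44 or 59 per group reaches 80%. Adjustment for baseline could close the gap, but with 37 per group only at a correlation near 0.7, which the article does not claim.

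These figures assume independent women, equal groups, a t test and d = 0.42 as stated; the adjusted figures also assume a raw-value SD. The individual-level formula makes no allowance for assignment by health center, three to each arm. Power for the primary outcome cannot be judged from the article.

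**What to change.** 1. Withdraw the statement that 37 per group gives 80% power, and do not relabel 37 as the number for a paired test.
2. Reconcile 59, 44 and 26 per group, and say which is the planned size and which the achieved size.
3. At that size, restate power for the between-group comparison. Either give the unadjusted figure, or give it for the planned ANCOVA or difference-in-differences with the assumed baseline correlation stated and a range shown. Say whether 30.68 is an SD of raw values or of changes.
4. Label the calculation as applying to 8-OHdG, a secondary outcome. Say that power for Pb, Cd and Hg was not established, and interpret those results through confidence intervals.

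The cost is one rewritten paragraph and a stated power that is likely to look less favourable. The correction does not in itself decide whether enrolment should continue or stop.

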## Methods

### Study Design

This study is an ongoing quasi-experimental investigation that uses a nonrandomized pre-post test methodology. Expectant mothers were divided into 2 cohorts, one receiving an intervention and the other serving as a control. This study applied a nonrandomized pre-post test design due to practical considerations related to (1) practical management, (2) geographical differences, and (3) time constraints.

First, practical management considers that managing the study is easier when specific locations are designated for the intervention group and other locations for the control group. This approach ensures that the intervention (*M. oleifera* supplementation) can be efficiently delivered and monitored in each location without the complexity of randomizing participants across multiple sites. Furthermore, grouping participants by location helps streamline logistical operations such as monitoring compliance and ensuring consistent follow-up over the course of the intervention period.

Second, although the geographical settings of the intervention and control groups may differ, they were comparable in terms of demographic characteristics and environmental conditions. This allowed us to evaluate the effects of moringa supplementation in different geographical settings while maintaining comparability between groups. In addition, by focusing on distinct locations for intervention and control, we ensure better resource allocation and minimize the logistical challenges that would arise from attempting to randomize participants across a broader region.

Third, time was considered a constraint due to limitation in the laboratory. We could not receive heavy metal analysis results from the initial screening at the same time for all participants. Therefore, women with high levels of heavy metals at the first screening were included in the intervention group to avoid delays. This ensures that these participants can begin the 2-month intervention with *M. oleifera* as soon as possible after obtaining the result, considering the limited research timeframe. Furthermore, because we limited the overall time for the study, randomizing participants could cause delays in implementing the intervention and complicate the process of ensuring that those with high levels of heavy metals receive timely treatment.

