### Participant Recruitment

This research has been conducted in Makassar City, specifically at 6 community health centers where expectant women receive prenatal services. The 6 selected community health centers are located in areas with varying environmental characteristics, including industrial zones, regions near landfill sites, and coastal areas. While the types of pollution sources differ, all sites share a common feature: exposure to potential environmental contaminants. Each represents an urban setting with a plausible risk of heavy metal exposure through air, water, and food pathways. Thus, despite differences in specific pollution types, the study sites are considered comparable in terms of overall environmental risk exposure. This selection strategy ensures that the intervention and control groups are drawn from communities facing similar environmental health challenges. Moreover, such variation may enhance the generalizability of findings across different urban pollution contexts. Three centers were assigned as intervention sites and 3 as control sites based on operational convenience and to avoid information spillover between groups.

The study will include 59 pregnant women in each group of intervention and control who underwent an examination at health centers in Makassar and fulfilled the following inclusion criteria: (1) pregnancy during the second or third trimester, (2) intention to deliver in Makassar, (3) living in Makassar for a period exceeding 1 year, and (4) blood levels of Hg, Pb, or Cd exceeding the reference value. Participants will be excluded based on self-report during interview if they (1) are having twin pregnancy, (2) had known chronic medical conditions, such as diabetes, cancer, kidney diseases, (3) are taking other antioxidant or mineral supplements beyond standard care, (4) are diagnosed with micronutrient deficiencies, (5) relocate during the intervention period, and (6) are unwilling to comply with follow-up procedures.

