### Intervention Group

In addition to receiving iron capsules, which are standard supplements provided by the health centers as part of the national prenatal care program, participants in the intervention group also received *M. oleifera* extract supplementation at a dose of 2000 mg/day, administered as 2 capsules taken twice daily (totaling 2000 mg/day) for a continuous period of 8 weeks. Supplementation began immediately upon enrollment, which occurred between gestational weeks 20 and 32. Therefore, the regimen lasted from the time of enrollment until 8 weeks later, typically ending between weeks 28 and 40 of gestation. For participants enrolled in the late third trimester who delivered before completing the full 8 weeks, they were instructed to continue consuming the remaining *M. oleifera* supplements until the full course was completed. This approach aimed to ensure consistency in the intervention dosage, regardless of the timing of delivery, and to maintain the study’s internal validity.

To support adherence, we collaborated with health cadres at each participating health center. The cadres will be responsible for supervising, reminding, and ensuring that the mothers consistently take the moringa capsules. A WhatsApp group was established specifically for the cadres to facilitate regular communication, provide reminders, and monitor the supervision process throughout the 8-week supplementation period. We have also added a simple adherence log that will be maintained by the cadres, documenting capsule intake daily based on direct questioning or observation. These dual approaches—cadre monitoring and pill counts—will allow us to triangulate adherence data and better distinguish true intervention effects from variability due to compliance.

Participants will be actively monitored for adverse events throughout the 8-week intervention period. At the follow-up visit, participants will be asked about any symptoms or side effects experienced, using a structured checklist and open-ended questions. Specific adverse events of interest include gastrointestinal discomfort (nausea, vomiting, and diarrhea), allergic reactions (skin rash and swelling), and general intolerance to the supplement.

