### Biomarker Analysis

#### Heavy Metal Analysis

The measurement was conducted to determine Hg, Pb, and Cd levels in the blood of pregnant women during the second or third trimester. Heavy metals were analyzed using inductively coupled plasma mass spectrometry (ICP-MS) (Thermo Fisher Scientific, Bremen, Germany) and performed in micrograms per liter. To ensure analytical accuracy and method validation, we used certified reference materials (CRM BCR®-636, lyophilized human blood, Joint Research Center-JRC, European Commission) as a quality control standard. For quality assurance and quality control (QA/QC), calibration curves were generated using multielement standard solutions of known concentrations. Blank samples were included in each analytical batch to monitor contamination.

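### Control follow-up sampling is tied to an antenatal visit, while intervention sampling follows a course that can run past delivery, so women who deliver early fall under different rules in the two arms

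*Protocol article*

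**What the plan says.** **Intervention arm.** The Intervention Group section says of women "who delivered before completing the full 8 weeks, they were instructed to continue consuming the remaining" capsules that they should do so to the end of the course. Capsule Supplement Production gives the same instruction. Data Collection puts the second measurement of metals, 8-OHdG and MDA at the close of the supplementation period, at 8 weeks. Participant Recruitment adds that this blood is drawn at a routine visit.

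**Control arm.** Participant Recruitment says: "Follow-up blood sampling was also conducted after 2 months, aligned with their next scheduled antenatal visit". It does not say what happens if a control has delivered by then.

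**Analysis.** Data Analysis allows last observation carried forward (LOCF) for missing follow-up outcomes where feasible, with sensitivity analyses under other missing-data assumptions. The ANCOVA covariates include gestational age. They do not include pregnancy status at the second draw.

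**Enrolment window.** The Intervention Group section states "Supplementation began immediately upon enrollment, which occurred between gestational weeks 20 and 32", with the course "typically ending between weeks 28 and 40 of gestation". The inclusion criterion reads "pregnancy during the second or third trimester" and sets no upper week.

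**The concern.** The primary outcome is the change in blood lead, cadmium and mercury between two draws, compared between arms by difference-in-differences and ANCOVA. That comparison is clean only if the second draw is taken under the same conditions in both arms.

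For a woman who delivers between the draws, the written rules part ways. Followed literally, they sample her postpartum if she is in the intervention arm and give her no sampling occasion if she is a control. Any change in blood concentrations that accompanies delivery, or any zero change imputed for a missed control, would then enter the arm contrast and be read as an effect of moringa. Gestational age as a covariate adjusts for a differing chance of having delivered. It cannot adjust for the two arms handling the same event differently.

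**Working it through.** **1. The plan's own window.** Enrolment week plus 8 gives 20 + 8 = 28 and 32 + 8 = 40. The stated end of course, weeks 28 to 40, is reproduced. Its upper end lies in the weeks when delivery is expected, so some women will deliver before the second draw.

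**2. The rules side by side for a woman who delivers before week 8.**

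| | Intervention | Control |
|---|---|---|
| Instruction after delivery | Finish the course | None stated |
| Second draw | End of the course, routine visit | After 2 months, at an antenatal visit |
| Consequence | Postpartum sample implied | Missed, sampled early, or sampled outside the rule; not stated |

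**3. How many women.** The documents give no distribution of delivery week, so this step rests on assumptions: delivery week normal with mean μ and SD σ, and enrolment week g uniform. For a woman undelivered at g, the chance of delivery before g + 8 is

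[Φ((g + 8 − μ)/σ) − Φ((g − μ)/σ)] / [1 − Φ((g − μ)/σ)],

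averaged over g. As an example, with g = 32, μ = 39 and σ = 1.8 the first term is Φ(1/1.8) = 0.711 and the other terms are negligible.

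| μ, σ (weeks) | Enrolled 20–32 | Enrolled 28–32 | Enrolled at 32 |
|---|---|---|---|
| 39.5, 1.5 | 7.4% | 21.9% | 63.1% |
| 39, 1.8 | 11.1% | 32.3% | 71.1% |
| 38.5, 2.0 | 14.7% | 41.5% | 77.3% |

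Over the stated window this is about 7 to 15%. With the 26 women per group reported so far, 26 × 0.074 = 1.9 and 26 × 0.147 = 3.8, so 2 to 4 per arm. With the 59 per group given in Participant Recruitment, 59 × 0.074 = 4.4 and 59 × 0.147 = 8.7.

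**4. The window itself is not settled.** The Intervention Group section also speaks of "For participants enrolled in the late third trimester who delivered before completing the full 8 weeks", which does not fit an enrolment limit of week 32. If, purely as an illustration, enrolment were uniform over weeks 20 to 36, the same formula gives 28 to 34% affected.

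**5. Illustrative bias.** If every early deliverer is sampled postpartum in one arm and none in the other, spurious difference = share × postpartum shift. For an assumed shift of 0.5 SD:
- enrolment at weeks 20–32: 0.074 × 0.5 = 0.04 SD to 0.147 × 0.5 = 0.07 SD;
- enrolment clustered at weeks 28–32: 0.219 × 0.5 = 0.11 SD to 0.415 × 0.5 = 0.21 SD.

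The planning effect is d = 0.42, although it was derived for 8-OHdG and not for metals.

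**6. Carrying baseline forward.** If a share p of controls is missed and carried forward, the control mean change becomes (1 − p) times its true value, provided the missed women would have changed by the arm's average. With p of 7 to 15%, the control change shrinks by 7 to 15%.

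**The case against.** The strongest reply is that no sentence says intervention women were sampled postpartum. Both arms have a nominal 2-month interval, and the asymmetry could be no more than loose wording about visits in a condensed article. A rule for delivered women may sit in the full protocol. It is true that postpartum sampling is an inference from two sections read together, and that the plan shows no observed imbalance. But the article does state a sampling rule for each arm, and the two rules diverge for the same woman. That is more than an omitted detail.

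Four stronger readings are tempting and are not supported:

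- *That the plan contradicts itself by declaring every sample to be taken in pregnancy.* Heavy Metal Analysis refers to "levels in the blood of pregnant women during the second or third trimester", but this echoes the inclusion criterion. It describes the population and is not a rule for the second draw.
- *That the arms have different draw-to-draw intervals.* Study Design says "We could not receive heavy metal analysis results from the initial screening at the same time for all participants", which describes staggered results. Elevated metals were an inclusion criterion for both groups, and nothing sets a different clock for each arm.
- *That delivered controls will be imputed as unchanged.* LOCF is allowed only where feasible, sensitivity analyses are planned, and the documents do not say whether such women were missed.
- *That postpartum blood differs by a known amount.* The Introduction cites values for early and late pregnancy that differ (mercury 2.37 and 1.95 μg/L, cadmium 0.62 and 0.70 μg/L), but gives nothing after delivery.

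It is also a fair objection that adding delivery status to the ANCOVA would be poor practice. Delivery is a post-baseline event that treatment could affect, and if no delivered control is sampled there is no overlap between arms from which to estimate its coefficient.

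**Conclusion.** The concern holds in a limited form. As written, the follow-up rules can mix pregnant and delivered women unequally between arms at the primary measurement, and nothing covers a control who has delivered. Under the stated assumptions about delivery week and even enrolment over weeks 20 to 32, about 7 to 15% of women are affected, or 2 to 4 of 26 per arm.

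The size and direction of any bias cannot be derived from the documents. With an assumed 0.5 SD shift and a complete split between arms it is about 0.04 to 0.07 SD, which is modest. The larger figures need late-clustered enrolment, which the plan does not state. A reader might infer that the primary result is already biased, but the documents show only that the rules permit it. The point should be corrected before analysis. It does not invalidate the comparison.

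**What to change.** Leave the supplementation course as it is, and change only sampling and analysis:

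1. Apply one follow-up interval, counted from the baseline draw, in both arms, whether or not the woman has delivered.
2. Record the sampling date and whether the woman was pregnant or delivered at the draw.
3. Report by arm how many women delivered before the second sample, and how many of those were sampled.
4. Do not carry baseline forward for women missed because they delivered. Handle them within the missing-data sensitivity analyses already planned.
5. Add a sensitivity analysis restricted, in both arms, to samples taken before delivery. Read it with caution, because it conditions on a post-baseline event.
6. Keep delivery status out of the primary ANCOVA.
7. Reconcile the statements on enrolment: the week 20 to 32 window (Capsule Supplement Production, Intervention Group), the mention of late third-trimester enrolment (Intervention Group), and the inclusion criterion (Participant Recruitment).

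The cost is two recorded items, one short table and one sensitivity analysis. Data collection began in July 2024 and the second laboratory step was under way by February 2025, so re-timing may no longer be possible for some or all women. For samples already taken, only recorded dates and analysis are needed.
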